### Procedures and Data Collection

#### Virtual Data Collection.

Once child eligibility is confirmed, baseline data collection occurs via a virtual zoom visit including: guided anthropometry [43] and neck circumference measurements, a child 24hr. dietary recall, registration for one-week of Ecological Momentary Assessment (EMA) on their phone [44], and training on video recording of family meals. Following the virtual visit, a 14-day observational period ensues including a parent online survey, two additional 24-hr dietary recalls, ten days of EMA measuring parent stress and parenting practices, and a 2-day video-recorded family meal observation period (1 weeknight, 1 weekend night) measuring family meal quality (i.e., dietary, interpersonal) [45]. Virtual data collection occurs at baseline, 6 months (post-intervention), and 12 months (6-month post-intervention). Primary and secondary outcome measures are described in Table 1 and are collected at all three data collection time points in all Arms. Virtual protocols are based on ours [37] and other’s [7,37] prior studies. Data collection tools and databases (i.e., REDCap) include features to support HIPAA compliance and allows for data checks to ensure data quality during data entry. Access to data collection tools and databases including REDCap and Box will be strictly limited and regulated through personal user profiles. Both of these platforms are password protected and all data will be regularly backed up into a password-protected database.

#### Measures.

This study has three primary child outcomes: BMI%ile [46], neck circumference [47], and diet quality [48,49]. Secondary outcomes include family meal quantity, meal dietary quality [21], meal interpersonal quality [50], parent outcomes: BMI [51], neck circumference [47], food-related parent practices [52], coping skills, sibling BMI%ile, and others [8,13,39,53–60] (see Table 1).

#### Blinding and Investigator Allocation Concealment.

As with most behavioral interventions, it is not possible to double blind this RCT. However, this study incorporates measurement staff and investigator blinding as much as possible to minimize bias. For example, the intervention is administered by CHWs who are not involved with measurement team responsibilities or meetings and measurement team members are blinded to participant study Arm assignment and are not involved with intervention team responsibilities or meetings. The biostatistician is the only completely unblinded member of the research team and will be overseeing data management and analyses throughout the trial and will have restricted access to the final study dataset.

#### Measurement Team Training and Supervision.

Measurement team members are trained, engage in role-plays, conduct mock visits, and are closely supervised by the measurement team director according to best practice [7,63]. Table 2 describes these processes in depth. All practice, certification, and data collection visits are video recorded to allow for thorough supervision of visits where both the measurement team member and their supervisor gives feedback.

Measurement team members are also trained on the Iowa Family Interaction Rating Scale (IFIRS) for video coding of family meals and the Nutrition Data System for Research *(NDS-R)* for dietary recalls [61]. Staff only code families in which they did not participate in the measurement visit [7,20,21]. Practice videos are used until coders reach 95% inter-rater reliability and 100% after consensus meetings; 25% of videos are double coded and checked at a 1:5 ratio to ensure high inter-rater reliability and fidelity to protocols. For *NDS-R*, quality assurance is conducted on 100% of recalls [64].

#### Retention Plan.

To minimize attrition in all study Arms, the following retention strategies are used, based on our successful prior studies with >95% retention rate and best practice [63,65]: (1) gather extensive participant contact information (e.g., phone numbers, email addresses, home/work addresses, emergency contacts); (2) tailor preferred forms of contact to participants (e.g., texts, phone, email); (3) utilize primary care electronic medical record (EMR) databases for updated contact information; (4) send tracking postcards during important cultural celebrations (e.g., Hispanic Heritage Month, Native American Heritage Day); and (5) use ongoing tracking databases (e.g., LexisNexis, White Pages). Additionally, at 9 months families are sent a small gift (e.g., reusable grocery bag with the *Family Matters* logo) and a short survey asking them to update their contact information.

#### Ethical Considerations.

The University of Minnesota’s Institutional Review Board (IRB) Human Subjects Committee approved all protocols used in the study. Prior to enrollment into the study, participants are provided with detailed information about the study by our research team via consent and assent forms including study aims and detailed procedures. Participants are informed that their participation is voluntary and that they have the right to withdraw from the study without any consequences at any point. They will be assured of anonymity in participation and confidentially of any data they provide throughout the study, through the use of study IDs and the storage of sensitive information in secure online platforms (i.e., REDCap and Box). Participants can be enrolled into the study only after they have provided written consent and assent forms to our research team.

#### Regulatory Oversight/Monitoring.

All study modifications will be communicated with and regulated by the IRB. Even though the study is expected to pose minimal risk, the Data Safety Monitoring Board (DSMB), in collaboration with the study investigators will closely monitor recruitment, process evaluation, and retention activities. The DSMB will meet yearly with the study investigators and staff, or more often as needed, for oversight of the study. Any adverse events will be reported to the NHLBI and the IRB at the University of Minnesota. This trial is also registered in the OnCore clinical trial management system and is audited by the Medical School at the University of Minnesota.

## INTERVENTION

The *Family Matters* three-arm intervention, known as the *Family Matters Program* to our study families, components and dose are described below.

### Study Arm #1: EMI

Parents randomized to study Arm 1 receive EMI text messages twice a day for 16 weeks via their smartphone. A study smartphone is provided for use if needed.

#### EMI.

Our prior research showed parental stress early in the day was associated with more controlling food parenting practices and serving more unhealthful foods (e.g., fast food) at dinner the same night [66]. Therefore, in all Arms, parents receive EMI text messages to their phones that include two parts. First, the parent is sent a text message with a survey link, between 11am-2pm to report their stress level (i.e., scale of 0-10) and sources of stress (e.g., child demands, busy at home/work, social media). Second, a text message is sent back to the participant from a bank of tips (approximately 50 tips per source of stress) for the particular source of stress they reported. This tailored tip is intended to help them cope with the reported stress and increase the likelihood that they will still carry out a family meal the same evening in the face of stress [66]. After the tip is sent, parents are also asked to report whether or not the tip was helpful, which then adjusts their individual EMI algorithm so there is an increased likelihood of them receiving more or less of these types of tips. If parents report no stress, they receive a tip to facilitate having a family meal (e.g., recipe ideas, meal prep tips, mealtime conversation starters).

### Study Arm #2: EMI+Virtual Home Visiting (HV) with CHW+Video Feedback

Parents randomized to study Arm 2 receive all elements of study Arm 1, in addition to home visiting by a CHW. Visits by CHWs are virtual via zoom and occur every-other-week (8 total) simultaneously with the 16 weeks of EMI. In between CHW home visits, families complete “Try-it-Yourself” activities (8 total) to reinforce new behaviors and meal preparation skills (e.g., batch cooking recipe, shopping scavenger hunt, stress reduction coping skills).

#### Home Visiting.

CHWs carry out the 60-90-minute HVs using Motivational Interviewing (MI) [67,68] and psychoeducation [35]. The visits focus on family meal quantity and quality factors [7,20,21] known to be associated with child CVH. Family members are taught specific skills through didactic and interactive session activities (e.g., AHA Slides, Figma games) to improve family meal processes and behaviors. Session content and activities are described in Table 3. A SMART goal (i.e., specific, measurable, achievable, relevant and time-bound) [69] is set at the end of each session related to the content delivered in the home visit and their video feedback.

#### Video Feedback.

Every other week, starting during home visit three, families video-record and upload one family meal via their smartphone (6 total meals). CHWs watch videos in between home visits to identify specific clips to show family members at the next visit that highlight both strengths and growth areas regarding interpersonal interactions and dietary patterns. During HVs, CHWs engage family members in a conversation–using MI skills [67] where both the CHW and family members identify positive behaviors seen in the videos and areas for growth, based on session content that families have been learning.

#### “Try-it-Yourself” Activities.

Families are given food-related (e.g., recipes, meal planning strategies) and interpersonal (e.g., food prep with kids, family meal communication game, stress reduction) activities to try out in between visits to increase their self-efficacy in preparing family meals on their own and reinforce messages they are taught during HVs. The study child and all siblings in the home are also given an activity book with games that reinforce session content.

### Study Arm #3: EMI+Hybrid HV with CHW+Video Feedback

Parents randomized to study Arm 3 receive all elements of study Arm 2, but they are delivered hybrid. Specifically, CHWs meet in-person with families every other HV and then virtually via zoom on the other weeks. Families also engage in two cooking demonstration activities with the CHW during in-person HVs to reinforce messages taught, share easy recipes (e.g., batch cooking, one ingredient for multiple meals), and teach food prep skills to increase family’s self-efficacy for having family meals. This Arm is important to examine whether relationship building and creating an atmosphere conducive to health behavior change requires an in-person component. This Arm is also critical to examine COVID’s impact on moving research to virtual modes.

### Maintenance Phase

After completing four months of the intervention, all study Arms transition to a two-month maintenance phase, based on best practice [70]. For all study Arms, EMI family meal tips are reduced to the three days per week that parents reported their highest stress levels during the 16-week active intervention phase. Stress profiles corresponding to the high risk stress days are created for each participant to maximize intervention uptake and subsequent sustainability [24,25].

### Process Evaluation

A robust feasibility and process evaluation protocol was designed for this intervention (see Table 4), to ensure feasibility, generalizability, and dissemination into primary care and other health care settings [70,71].

## STATISTICAL ANALYSIS PLAN

### Overview.

This study is powered for three pairs of tests [72] to evaluate intervention effectiveness: (a) Arm 2 vs. 1, (b) Arm 3 vs. 1, and (c) Arm 2 vs. 3 over three time points. Multi-level, general linear mixed models (MLMM) with a clinic random intercept that nests participants within clinics to address any clinic differences in the recruitment populations, with participant random slopes for time to examine intervention treatment effects, and conditional fixed effects regression models (within-child analytic contrast against baseline), are the primary analytical models for all study hypotheses. Participants’ randomized condition will be examined irrespective of adherence to the study protocol in accordance with an intent-to-treat (ITT) analysis. After the intervention has been fully administered, data will be assessed for balance across arms, outliers, missingness, and other modeling assumptions. Although randomization is expected to produce balance on measured and unmeasured characteristics, variables will be considered for inclusion as controls in adjusted analyses to reduce test statistic variance [73]. We expect little missing data based on our prior work, but if needed, we will employ methods recommended for clinical trials to minimize analytical assumptions required when missing data are present (e.g., follow up all randomized participants prior to unblinding [74], evaluating if results from the primary analysis differ when sensitivity analyses are performed [75]). Reasons for participant withdrawal and non-adherence will be analyzed and reported in the final ITT analysis [76].

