### Study Arms and Randomization

Families are randomized into one of three intervention Arms: (1) EMI; (2) EMI+Virtual HV with a CHW+Video Feedback; and (3) EMI+Hybrid HV with a CHW+Video Feedback. All Arms receive 16 weeks (4 months) of EMI stress reduction and family meal tip messages via smartphones. Arms 2 and 3 additionally receive eight home visits by CHWs focused on family meal quantity and quality, a meal preparation activity, and video feedback on their family meal behaviors/patterns every-other-week for 16 weeks. Arm 2 receives all of these components virtually and Arm 3 receives these components half in person and half virtual (hybrid). In between weeks, families in Arms 2 and 3 complete a Try-it-Yourself activity to apply the new skills/behaviors they have been taught. All Arms receive an 8-week (2 months) maintenance phase allowing for progressively less support so they can increase self-efficacy and sustainability of behavior change.

Once participants complete their baseline data collection visit, they are randomized into one of three study Arms (n=175 per Arm). If households have multiple eligible children, one child is randomly selected to minimize bias that could affect generalizability due to parent selection. Randomization is stratified by five racial/ethnic groups (African American, Hispanic, Native American, Asian American, White; n≈105 per race group). Block randomization schedules were produced in PASS 2021 (Kaysville, Utah) to account for the racial/ethnic stratification. Schedules are maintained by the biostatistician to keep team members blinded.

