### Sample Size and Power Computations.

Study design features were accounted for in powering the study that required increases in sample size to minimize an inflated experiment-wise error rate (EER) due to three pairwise tests between each treatment arm for three primary outcomes (i.e., BMI%ile, neck circumference, and the Healthy Eating Index (HEI)). Accounting for these nine tests, sample size was determined using a conservative two-sided critical value of *z*=2.77 (*P*=0.006) to achieve experiment-wise Type I error of 0.05. Our power calculations were based on prior studies showing that a decline of two BMI%ile points was a clinically meaningful difference in children with overweight/obesity [46]. BMI%ile is a continuous outcome with a variance of 18.8. Eighteen-month follow up data with a comparable cohort provided intraclass correlation coefficient estimates to inform sample size determination (BMI%ile ICC ). At 80% power and multiple-outcome and pairwise testing corrected EER of 0.05, with a sample size of 525, we will be able to detect a minimum average difference in BMI%ile as small as 1.67 (or 0.38 SD) with 15% attrition. This magnitude translates to approximately a 2.8lb difference in a six year-old boy who is 3.8 feet tall and 45 lbs, or approximately a 7.5 ounce per month change in weight by the post-intervention endpoint.

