**Treatment Delivery**	
Ensure adherence to intervention protocol with regard to content and treatment dose	· Video-record intervention sessions, supervisor and self-evaluation e and review with the CHW interventionists (video-feedback) · Code delivered sessions for fidelity to MI using the MITI coding manual and provide feedback to CHW interventionists
Reduce differences in intervention delivery	· Use scripted intervention protocol and session materials · Have supervisors evaluate video-recorded delivered sessions using a MI-specific guide and pre-developed session specific checklists · Code delivered sessions for fidelity to MI using the MITI coding manual
Control for CHW interventionists differences (i.e., assess nonspecific treatment effects)	· Assess participant’s relationship with the CHW interventionists via mid and end of intervention surveys and provide feedback to CHW interventionists · Have supervisors evaluate video-recorded delivered sessions using MITI coding system · Have CHW interventionists work with all intervention Arms

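### The primary models have no community health worker term, so standard errors against Arm 1 will be too small if outcomes correlate within worker

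*Protocol article*

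**What the plan says.** The Overview of the statistical analysis plan names the random terms of the mixed model: participant slopes for time and "a clinic random intercept that nests participants within clinics to address any clinic differences in the recruitment populations". It pairs this model with a conditional fixed-effects regression that contrasts each child with baseline, and says that these "are the primary analytical models for all study hypotheses". The planned contrasts are "a) Arm 2 vs. 1, (b) Arm 3 vs. 1, and (c) Arm 2 vs. 3 over three time points". The power section sets a critical value of 2.77 to protect against error inflation "due to three pairwise tests between each treatment arm for three primary outcomes", nine tests in all.

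On delivery, Study Arms and Randomization says that "Arms 2 and 3 additionally receive eight home visits by CHWs focused on family meal quantity and quality". The Arm 1 section describes text messages only: "Parents randomized to study Arm 1 receive EMI text messages twice a day for 16 weeks". Table 4, under Treatment Delivery, lists control of differences between CHWs as a goal. Its means are relationship surveys, supervisor ratings and the instruction "Have CHW interventionists work with all intervention Arms". None of these is an analysis term.

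**The concern.** Families seen by the same CHW share that worker's skill and style over eight visits of 60 to 90 minutes with goal setting and video feedback. Any resulting correlation arises after randomisation and only in Arms 2 and 3, so the design is partially nested.

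The stated terms do not pick this up:

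- The clinic intercept deals with recruitment differences, which individual randomisation already tends to balance.
- Participant slopes are separate for each child, so they carry no correlation between families.
- The within-child contrast removes stable differences present at baseline, not an effect that the CHW introduces later.

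At stake is the experiment-wise error of 0.05 that the trial set its critical value to protect. The planned detectable difference against Arm 1 would also be optimistic.

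**Working it through.** **Inputs from the article.** 175 children per arm; 15% attrition, so 175 × 0.85 = 148.75 completers per arm; variance of BMI percentile 18.8 (SD 4.336); z = 2.77, two-sided level 0.0056; 80% power; three contrasts by three outcomes, of which 2 × 3 = 6 tests involve Arm 1.

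**Assumed, because not given.** Number of CHWs K from 6 to 16; CHW ICC ρ from 0.01 to 0.05; equal caseloads; one CHW per family; CHWs crossed over Arms 2 and 3.

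**The plan's own figure.** Detectable difference = (2.77 + 0.8416) × 4.336 × √(2/175) = 1.674, or 0.386 SD. This matches the stated 1.67 (0.38 SD) with 175 independent children per arm, so no CHW allowance is visible. The ICC value is lost from the text, so what the calculation allowed for cannot be fully audited. With 148.75 per arm the same formula gives 1.82 (0.42 SD). That gap is a separate attrition question and is not attributed to CHWs here.

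**Contrasts with Arm 1.** Families per CHW per arm: m = n/K. Design effect in the CHW arm: DE = 1 + (m − 1)ρ. True SE over model SE: r = √((1 + DE)/2). Actual level: p = 2(1 − Φ(2.77/r)). Sum over nine tests: 6p + 3 × 0.0056. With n = 148.75:

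| K | ρ | m | DE | r | p | sum of nine |
|---|---|---|---|---|---|---|
| 16 | 0.01 | 9.3 | 1.08 | 1.021 | 0.0066 | 0.057 |
| 16 | 0.05 | 9.3 | 1.41 | 1.099 | 0.0117 | 0.087 |
| 10 | 0.01 | 14.9 | 1.14 | 1.034 | 0.0074 | 0.061 |
| 10 | 0.05 | 14.9 | 1.69 | 1.161 | 0.0170 | 0.119 |
| 6 | 0.01 | 24.8 | 1.24 | 1.058 | 0.0088 | 0.070 |
| 6 | 0.02 | 24.8 | 1.48 | 1.113 | 0.0128 | 0.094 |
| 6 | 0.05 | 24.8 | 2.19 | 1.263 | 0.0283 | 0.186 |

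At ρ = 0 the level stays at 0.0056. Simulation supports the formula: with 175 per arm, 8 CHWs and ρ = 0.05, the simulated level was 0.025, as the formula gives.

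**Arm 2 vs 3.** If the same CHWs serve both arms equally, their main effect cancels and the SE ratio is √(1 − ρ), or 0.995 to 0.975: slightly conservative. If CHWs were instead nested in arm, the ratio would be √DE. With 8 per arm, ρ = 0.05 and n = 148.75 that is 1.371 and a level of 0.043. CHW-by-arm variance also breaks the cancellation: with 8 CHWs, 0.03 of variance for the main effect and 0.02 for the interaction, the simulated level was about 0.02.

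**Detectable difference against Arm 1.** On the basis that reproduces the plan (175 per arm, z = 2.77):

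- 16 CHWs, ρ = 0.01: m = 10.94, DE = 1.099, r = 1.025, so 0.386 × 1.025 = 0.40 SD.
- 6 CHWs, ρ = 0.05: m = 29.17, DE = 2.41, r = 1.305, so 0.386 × 1.305 = 0.50 SD.

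Small-sample degrees of freedom cost more. By Satterthwaite, df = (1 + DE)² / (1/(n − 1) + DE²/(K − 1)). For 6 CHWs, ρ = 0.02 and n = 148.75: 2.476² / (0.0068 + 0.4357) ≈ 14. The critical value becomes 3.27, and the detectable difference is 0.53 SD rather than 0.47 with z. At ρ = 0.05 it is 0.64 rather than 0.53.

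**The case against.** **A reader might infer that the six standard errors are definitely too small.** The documents do not support that. It needs a CHW ICC above zero, and neither the ICC nor the number of CHWs is given. With 16 CHWs and ICC 0.01 the effect is trivial. This objection stands, and the point is therefore conditional.

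**If the visits change no child's outcome, they induce no CHW variance and the level is not inflated.** This is correct. Inflation under the null needs CHW effects that differ but average zero, and inference to CHWs beyond those employed. The article's aim of dissemination to other primary care settings makes that inference reasonable, but it is a choice of target.

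**The summed level overstates experiment-wise error.** It does, because the tests share Arm 1 and the CHWs. For 6 CHWs and ICC 0.02 the sum is 0.094. Simulation gave about 0.08 with uncorrelated outcomes and about 0.07 with outcome correlation 0.5. An excess over 0.05 remains.

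**A condensed article may leave interventionist effects to a full analysis plan.** This would carry weight if the article were silent. It names its random terms and calls the models primary, so the omission lies in a stated analysis.

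**A reader might infer from Table 4 that CHWs also serve Arm 1, or that crossing them controls the problem throughout.** The table concerns fidelity, and its wording is naturally read as the CHW-delivered arms. Crossing helps Arm 2 vs 3 only. Scripting, common training and supervision may shrink CHW variance but do not model it.

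**Conclusion.** The structural point holds: the stated primary models account for clinic and participant but not for CHW, which is where treatment-related clustering can arise. Six of the nine primary tests are exposed if outcomes correlate within CHW. All nine would be exposed if CHWs are not shared across Arms 2 and 3, or if their effects differ by arm.

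The size is uncertain. Over the assumed range the level against Arm 1 lies between about 0.007 and 0.03 instead of 0.0056, and the upper bound on experiment-wise error between about 0.06 and 0.2. These figures also assume one CHW per family, which the arm descriptions suggest but do not fix. Because the magnitude rests wholly on assumed inputs and can be near-trivial, this is a should-fix.

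**What to change.** Before any outcome is compared between arms:

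- Add a CHW random effect confined to Arms 2 and 3 (partially nested, crossed over those two arms), with small-sample degrees of freedom.
- Make sure CHW identity is recorded for each family and visit. Table 4 says that visit details are tracked in REDCap but does not name this item.
- Report the CHW ICC, and state the detectable difference against Arm 1 over a range of ICCs and the actual number of CHWs.
- As an editorial matter, reword the Table 4 item to name Arms 2 and 3.

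No extra participants or visits are needed. The price is wider intervals against Arm 1: small with many CHWs and an ICC near zero, but possibly marked with few CHWs and a larger ICC, as the small-sample figures show. Half of the CHWs speak Spanish. If families are matched to CHWs by language, which the article does not say, the CHW term will also absorb language or ethnic differences between caseloads, and the plan should say how it separates the two.

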#### Aim 1 (Primary Outcomes): Examine intervention effects on markers of child CVH including BMI%ile, diet quality, neck circumference.

Treatment condition mean differences on the three primary outcomes will be examined at the post-intervention primary endpoint (6 months after baseline). Sample size determination allows for primary outcome standardized effect size assessment of all three outcomes of at least 0.38, which is a small-to-moderate minimum detectable effect.

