**Child Diet Quality**	Child diet quality was used as a primary outcome given its link to child risk for heart disease and obesity in adulthood. **Procedure:** Three 24-hour dietary recalls (2 weekdays, 1 weekend day) [48] are conducted using the *Nutrition Data System for Research (NDS-R)* [61] regarding the child’s dietary intake. Following best practice guidelines [61], recalls for children <6 years old are done with only the parent. For children >6 years old, recalls are done with both the child and parent; the parent is the main reporter for children 6-8 years old, and the child is the main reporter for children 9+ years old [48]. **Measure:** The first recall is conducted during the virtual visit, and the 2^nd^ and 3^rd^ recalls are scheduled and conducted virtually during the 2-week period following the virtual visit. To increase accuracy of reporting, families are sent a Food Amounts Booklet to measure amounts, school lunch menus are utilized, and parents/children are encouraged to complete a food diary prior to the scheduled recall. An overall *Healthy Eating Index* (*HE*I) [49] score that measures overall diet quality/healthfulness will be calculated for analyses using data from 24-hour dietary recalls.
Secondary Outcome Measures	

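### The 0.38 SD detectable effect is carried from BMI%ile to every outcome, but under the within-child primary model it depends on each outcome's own baseline correlation, which is not given for the diet score (HEI); a baseline-adjusted analysis should decide

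*Protocol article*

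**What the plan says.** The Overview of the Statistical Analysis Plan section lists two model families as primary. One is a multi-level mixed model with a clinic random intercept and participant random slopes for time. The other is given as "conditional fixed effects regression models (within-child analytic contrast against baseline), are the primary analytical models for all study hypotheses". It does not say which of the two decides, or how the mixed model treats baseline.

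Under Sample Size and Power Computations, "sample size was determined using a conservative two-sided critical value of" 2.77, chosen for nine tests "to achieve experiment-wise Type I error of 0.05". The outcome input is that "BMI%ile is a continuous outcome with a variance of 18.8", and intraclass correlation estimates from a comparable cohort are said to have informed the calculation. The BMI%ile value is blank in the text as read. The result is a "minimum average difference in BMI%ile as small as 1.67 (or 0.38 SD) with 15% attrition".

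The Aim 1 paragraph describes the test as arm mean differences at 6 months and states: "Sample size determination allows for primary outcome standardized effect size assessment of all three outcomes of at least 0.38". The Aim 2 paragraph makes a similar claim for the family, parent and sibling outcomes. Table 1 bases the diet score on "Three 24-hour dietary recalls (2 weekdays, 1 weekend day").

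**The concern.** A standardised detectable effect can be carried from one outcome to another only if the analysis has the same relative precision for both. That is true of a comparison of follow-up means alone. It is not true of a within-child contrast, where the variance of the change is 2(1 − r) times the variance of a single measurement and r belongs to the outcome concerned. A figure that holds for BMI%ile need not hold for a diet score built from three recall days, because day-to-day variation enters at baseline and again at 6 months.

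At stake is the power for one of the three primary outcomes, and for any Aim 2 outcome with low repeatability. There is also a loss of precision that need not be accepted: a change contrast is never more precise than adjusting for the same baseline value as a covariate.

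**Working it through.** **Inputs.** From Sample Size and Power Computations: critical value 2.77, power 80% (normal quantile 0.8416), variance 18.8 (SD = √18.8 = 4.336) and attrition 15%. From Study Arms and Randomization: 175 per arm, hence 175 × 0.85 = 148.75 after attrition. The target effect is 1.67/4.336 = 0.385 SD, printed as 0.38. The correlation r for HEI is not in the document, so every value of r below is an assumption. Clinic effects and the 12-month visit are ignored.

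**Step 1: the plan's own figure.** For a comparison of 6-month means without baseline, the detectable effect is (2.77 + 0.8416) × √(2/n).

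- n = 175: 3.6116 × 0.1069 = 0.386 SD, or 1.674 points. This matches 1.67, but with no attrition.
- n = 148.75: 3.6116 × 0.1160 = 0.419 SD, or 1.816 points. This does not match; power for 1.67 points is 71%.

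With attrition kept, two other formulas return 1.67. The squared ratio needed is (0.3852/0.4188)² = 0.846.

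- Change score: 2(1 − r) = 0.846 gives r = 0.577.
- Baseline as covariate (ANCOVA): 1 − r² = 0.846 gives r = 0.393.

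The formula behind 1.67 therefore cannot be identified from the article.

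**Step 2: the r that the within-child contrast needs.** Its detectable effect is the Step 1 value times √(2(1 − r)). To reach 0.385 SD:

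- n = 175: r of at least about 0.50
- n = 148.75: r of at least about 0.58

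**Step 3: comparison with baseline adjustment.** The variance factor for baseline adjustment is 1 − r². The difference 2(1 − r) − (1 − r²) equals (1 − r)², which is never negative. Baseline adjustment is therefore at least as precise at every r.

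**Step 4: size.** Power at 0.385 SD is Φ(0.385/√(2f/n) − 2.77), with f = 2(1 − r) for the within-child contrast and f = 1 − r² for baseline adjustment. For example, at r = 0.3 and n = 175, f = 1.4 and √(2.8/175) = 0.1265, so Φ(3.044 − 2.77) = 61%.

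| Assumed r | Within-child power, n = 175 / 148.75 | Baseline-adjusted power, n = 175 / 148.75 | Within-child detectable effect (SD), n = 175 / 148.75 | Baseline-adjusted detectable effect (SD), n = 175 / 148.75 |
|---|---|---|---|---|
| 0.3 | 61% / 51% | 84% / 76% | 0.457 / 0.496 | 0.368 / 0.399 |
| 0.4 | 70% / 60% | 88% / 80% | 0.423 / 0.459 | 0.354 / 0.384 |
| 0.5 | 80% / 71% | 92% / 86% | 0.386 / 0.419 | 0.334 / 0.363 |
| 0.6 | 90% / 83% | 96% / 92% | 0.345 / 0.375 | 0.309 / 0.335 |
| 0.7 | 97% / 94% | 99% / 97% | 0.299 / 0.324 | 0.276 / 0.299 |

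**The case against.** Several points on the other side carry weight.

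- **The within-child model is only one of two.** The mixed model is named first, the Aim 1 test is described as a difference in 6-month means, and the Overview allows covariates to reduce variance. Baseline handling may be settled in a fuller plan that is not shown. This stands, and it is why the point is not that the trial is committed to a change score. It does not remove the point. A mixed model with baseline means left free in each arm gives, with complete data, essentially the same change contrast. The article itself calls the within-child model primary for every hypothesis.
- **The source of 0.38 SD.** A reader might infer that it came from a formula ignoring baseline, because that formula returns 1.674 points. The document does not support this. It names no formula, says that correlation estimates were used, and includes 15% attrition, under which that formula gives 1.82 points. The figure may already be a within-child calculation for BMI%ile. The missing correlation value may be a loss in text extraction and is not held against the plan.
- **Failure for HEI.** A reader might also infer that the trial is underpowered for diet quality. No HEI correlation is given, so this cannot be shown. With r at 0.6 or above, the within-child contrast exceeds 80% power even after attrition.
- **Baseline adjustment is not a full rescue.** At r = 0.3 after attrition it gives 76%, so 0.385 SD is missed there too. This stands.

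**Conclusion.** The point holds in a limited form. The 0.38 SD claim for HEI, and likewise for neck circumference and the Aim 2 outcomes, rests on correlations that the article does not show and on an unstated choice between two primary models. Under the within-child model the claim needs r of about 0.50 with full follow-up, or about 0.58 with the stated attrition. For HEI it is therefore unsupported, not refuted.

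The size of any shortfall depends entirely on the assumed r. Across r = 0.3 to 0.5, within-child power after attrition is 51% to 71%, against 76% to 86% with baseline adjustment. The preference for baseline adjustment does not depend on r, because it is at least as precise at every value; only the size of the gain does. BMI%ile and neck circumference stand to lose little if their correlations are high, which is also an assumption.

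**What to change.** In the Overview, make a baseline-adjusted comparison of 6-month means the deciding primary analysis for the three primary outcomes and the Aim 2 outcomes. Use either ANCOVA on the baseline value of the same outcome, or the mixed model already named with baseline means constrained equal across arms. Keep the within-child fixed-effects model as a sensitivity analysis only.

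In Sample Size and Power Computations and the Aim 1 and Aim 2 paragraphs, restate the detectable effect for each outcome under that model, at the post-attrition sample size and with the assumed r printed beside it. Do not describe 0.38 SD as the figure for a comparison that ignores baseline: with 15% attrition that figure is 0.42 SD (1.82 points).

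The cost is some rewording of the analysis plan. Baseline values are already collected in all arms, so no participants or visits are added. The stated detectable effect for a low-correlation outcome may become slightly less favourable, for example about 0.40 SD at r = 0.3 after attrition.
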